**Methods/design:**

Patients: Previously untreated girls and boys with idiopathic scoliosis, 9 to 17 years of age with at least one year of remaining growth and a curve Cobb angle of 25–40 degrees will be included. A total of 135 participants will be randomly allocated in groups of 45 patients each to receive one of the three interventions.

Interventions: All three groups will receive a physical activity prescription according to the World Health Organisation recommendations. One group will additionally wear a hyper-corrective night-time brace. One group will additionally perform postural scoliosis-specific exercises.

Outcome: Participation in the study will last until the curve has progressed, or until cessation of skeletal growth. Outcome variables will be measured every 6 months. The primary outcome variable, failure of treatment, is defined as progression of the Cobb angle more than 6 degrees, compared to the primary x-ray, seen on two consecutive spinal standing x-rays taken with 6 months interval. Secondary outcome measures include the SRS-22r and EQ5D-Y quality of life questionnaires, the International Physical Activity Questionnaire (IPAQ) short form, and Cobb angle at end of the study.

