### Randomisation

Randomisation will be done in a 1:1:1 ratio. A computer generated random numbers table in varying block sizes will be prepared a priori by an independent statistician. To conceal randomisation, the same independent statistician will prepare consecutively numbered, sealed opaque envelopes. The envelopes will be kept in a locked location. The envelope is to be opened in the presence of at least two persons. The original randomisation list will be kept by the independent statistician. One additional copy of the randomisation list is kept in a locked safe at the Karolinska Institutet, and not accessible for the research personnel.

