#### ***Primary outcome measures***

• The primary outcome variable, failure of treatment, is defined as progression of the Cobb angle more than 6 degrees, compared to the primary x-ray, seen on two consecutive spinal standing x-rays taken with 6 months interval [22].

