### Sample size

Based on figures from previous literature, a failure rate of 45% in the self-mediated physical activity group and a 15% failure rate in the brace and scoliosis specific exercise groups is hypothesised. Given a significance level of 5%, a power of 80% and consideration for dropout of up to 20%, an estimated 45 patients are required in each of the intervention groups.

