### Data analysis

Data from the different groups will be compared based on the 'intention to treat' principle. An intention to treat (ITT) analysis means that all patients, regardless of noncompliance, loss to follow-up or drop-out, remain in the analysis of the group to which they were randomised [27]. Multiple imputation of missing data will be used in the ITT analysis. A sensitivity analysis will be performed comparing the ITT data against a per-protocol data exclusively from patients who complied with the study protocol. If a patient in the study receives full-time bracing or surgery due to treatment failure, the Cobb angle at the moment of commencing this treatment will be considered in the secondary outcome analysis of Cobb angle.

Categorical parameters will be compared by the Chi-square test. Continuous and discrete parameters will be measured using parametric or non-parametric tests (depending on skewness) for group comparisons. Individual variables will be tested for their association with treatment effect by adding a predictor × treatment group interaction term to a regression equation. Additionally, Kaplan-Meier survival analyses will be used to display the probability of more than 6 degree Cobb progression over time for each group.

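### Kaplan-Meier curves will generally show a higher failure probability than the trial's own failure proportion if patients reaching skeletal maturity are censored (minor)

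*Protocol article*

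**What the plan says.** The Data analysis section names both a method and the quantity it is to show: "Kaplan-Meier survival analyses will be used to display the probability of more than 6 degree Cobb progression over time for each group". It presents this as an addition to the group comparisons, in which categorical outcomes are tested by chi-square under intention to treat with multiple imputation.

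The Abstract fixes when observation stops: "Participation in the study will last until the curve has progressed, or until cessation of skeletal growth". End of study repeats this and defines maturity by body-height growth of less than 1.0 cm in 6 months. Inclusion criteria ask for at least one year of remaining growth, with no upper limit, at ages 9 to 17. Maturity will therefore come at different times in different patients.

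The primary outcome is binary: "failure of treatment, is defined as progression of the Cobb angle more than 6 degrees, compared to the primary x-ray", confirmed on two consecutive films 6 months apart. Sample size assumes "a failure rate of 45% in the self-mediated physical activity group and a 15% failure rate in the brace and scoliosis specific exercise groups". No passage states how a patient who matures without failure enters the Kaplan-Meier curve.

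**The concern.** A patient who reaches maturity without confirmed progression has completed the trial's risk period and counts as a non-failure. Kaplan-Meier in its ordinary form removes that patient from the risk set as censored. It then in effect assigns the failure risk seen later among patients who are still growing. The complement of the curve therefore describes a setting in which growth, and with it exposure to the endpoint, never ends. That is not the proportion of the randomised group that fails.

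At stake is the reading of a published figure. One report could give two failure probabilities for the same event, the higher one in the curve, and readers may take absolute risks and risk differences from the curve.

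**Working it through.** **The plan's own figure.** Inputs from Sample size: 45% versus 15%, significance level 5% (taken as two-sided), power 80%, dropout up to 20%. Pooled mean = 0.30.

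n = [1.96 × √(2 × 0.30 × 0.70) + 0.842 × √(0.45 × 0.55 + 0.15 × 0.85)]² / 0.30² = 35.4, so 36; and 36 / 0.80 = 45.

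This reproduces the stated 45 per group. The calculation treats 45% and 15% as simple proportions failing, which is the quantity a curve of failure probability ought to reach.

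**Direction.** At 6-month visit j, let h_j be the proportion of those at risk who fail and m_j the proportion of the remainder who exit at maturity. Write S_j = ∏(1 − h_i) and M_j = ∏(1 − m_i), both over i ≤ j.

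- Kaplan-Meier complement, maturity censored: Σ h_j S_{j−1}
- Cumulative incidence, maturity competing: Σ h_j S_{j−1} M_{j−1}

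Since M_{j−1} ≤ 1, the first is never below the second. They are equal only if no failure occurs after the first maturity exit.

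**Size.** The article gives neither maturity times nor risks per visit, so what follows is assumption. Let maturity fall with equal probability at visits K = 2 to 6 (12 to 36 months), independently of progression, with no dropout.

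*Constant risk h per visit.* Solve mean over K of [1 − (1 − h)^K] = 0.45 or 0.15. This gives h = 0.144 and h = 0.0402. At 36 months the Kaplan-Meier complement is 1 − (1 − 0.144)^6 = 0.607 and 1 − (1 − 0.0402)^6 = 0.218.

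*Linearly declining risk,* h_k = c(7 − k)/6. Solving the same condition gives c = 0.1965 and 0.0563. The complement at 36 months is 0.524 and 0.182.

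| Maturity spread | Constant risk | Linearly declining risk |
|---|---|---|
| 12–24 months | 56% / 20% | 50% / 17% |
| 12–36 months | 61% / 22% | 52% / 18% |
| 12–48 months | 63% / 23% | 54% / 19% |

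The true values are 45% / 15% in every cell. For 12–36 months the 30-point difference is displayed as 60.7 − 21.8 = 38.9 points, or 52.4 − 18.2 = 34.2 points.

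*Later first failure.* If no failure can be recorded before 12 months, because confirmation needs two films, the 12–36 month constant-risk case gives 66% / 24%. With risk falling by a factor of 0.6 per visit it gives 53% / 19%. Across further maturity patterns under this convention the range is 52–75% and 18–29%.

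*No gap.* If all failures occur by 12 months, before anyone has left at maturity, or if all patients mature at the same visit, the complement equals 45% / 15%.

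**Where the gap lies** (12–36 months, constant risk, 45 per arm):

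| Month | Control: Kaplan-Meier vs cumulative incidence | Active: Kaplan-Meier vs cumulative incidence | At risk, control / active |
|---|---|---|---|
| 12 | 27% vs 27% | 8% vs 8% | 39 / 43 |
| 24 | 46% vs 41% | 15% vs 13% | 17 / 24 |
| 36 | 61% vs 45% | 22% vs 15% | 4 / 7 |

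At 24 months the arm difference is about 31 points against 28. The large discrepancy rests on the last few patients.

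**The case against.** The strongest reply is that censoring at maturity is inferred. The article states no censoring rule, and a condensed article may leave that to a fuller plan that is not shown. A plot that kept matured patients at risk as non-failures would end at the failure proportion. This stands as a limit on certainty. It does not dispose of the point, because the article names a method together with the quantity it is to display, and the usual form of that method does not estimate that quantity here.

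A second reply is that Kaplan-Meier with maturity censored answers a legitimate question: progression risk while still growing, freed from variation in remaining growth. Nor is maturity like death. Progression remains possible afterwards, and follow-up at 2, 5 and 10 years is planned. This also stands, but the article does not describe its curve in those terms.

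A reader might go further and infer that the curves are bound to contradict the primary result, that they are too high in every arm, or that the treatment comparison is biased. The documents do not support this. The gap can be zero, its size depends on risks the article does not give, and the primary comparison does not use the curve. The order of the arms was the same in every scenario calculated.

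**Conclusion.** The point holds as a minor one. If event-free patients are censored at maturity, the displayed failure probability cannot fall below the trial's failure proportion. It will generally exceed it, because entry criteria allow widely differing growth periods and failures can occur after the first exits. With maturity assumed evenly spread over 12 to 36 months, 45% / 15% would be shown as roughly 52–61% / 18–22% at 36 months, with most of the excess after 24 months. These sizes rest on assumed maturity times and risk patterns; only the direction follows from the design. The chi-square comparison, the sample size of 45 per group and the planned imputation are untouched.

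**What to change.** Replace the Kaplan-Meier sentence in Data analysis with one that displays cumulative incidence of treatment failure by group (Aalen-Johansen estimator), takes skeletal maturity without failure as the competing event, and censors only true loss to follow-up. With complete follow-up each curve then ends at the primary failure proportion. With dropout, small differences from the multiply imputed proportion may remain and should be noted. If a Kaplan-Meier curve is also kept, state that maturity is censored, label the curve as progression risk while still growing, and print numbers at risk beneath it.

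The cost is one or two sentences. The data, visits and tests do not change, and standard software produces the curve.

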## Discussion

The trial includes key methodological features that have been recognised as minimising bias in clinical trials: true randomisation, concealed allocation, specification of eligibility criteria, blind outcome assessment, blind analysis and intention-to-treat analysis. The nature of the treatments however precludes blinding of patient and treatment provided. Another potential source of bias is that there is no comparison of treatment groups to a randomised non-treatment control group to enable analysis of true effect of the treatments. This is because it can be considered unethical not to offer an active treatment to the eligible study population.

Our choice of outcomes is consistent with best practice recommendations for clinical trials studying AIS. The generalisability of future results may however be affected by our choice of bracing method. Our reasoning for using 3 dimensional hyper-corrective night–time bracing rather than full time bracing is that it may have potentially equivalent clinical effectiveness and possibly enable better compliance. It is also our clinical impression that the psychological concern for a teenager is much less when using a night-time brace compared to full-time use.

Another potential issue regarding generalisability is the content of the scoliosis specific exercise intervention. Some clinicians may advocate their preference for specific techniques based on their clinical experience or the limited scientific quality of previous studies. We have however taken an impartial approach to synthesizing a broad intervention covering principles outlined in scoliosis specific exercise literature. Future results from our scoliosis specific exercise protocol can only be generalised to the broad delivery of scoliosis specific exercise in an outpatient setting rather than generalised to individual techniques or application in an inpatient setting. Additionally, the study’s future results cannot be interpreted to suggest the potential efficacy of interventions involving both bracing and scoliosis specific exercise.

### Summary

This study uses a randomised controlled design to investigate the effectiveness of conservative treatments for preventing progression of AIS and the need for surgical interventions. The study also will investigate clinical features that may predict a patient's response to each treatment. The novel findings will enable evidence-based recommendations as to the effect of conservative interventions for AIS. Furthermore, findings will provide direction for future research into pathophysiological treatment rationale for the interventions.
